11.4 Data disclosure

11.5 Data safety and monitoring

11.6 Risk/benefit

11.6.1 Potential study risks

11.6.2 Potential study benefits

11.6.3 Risk/benefit assessment

## **1. Abstract**

The hepatitis C virus (HCV) is the leading cause of liver transplant and hepatocellular carcinoma in the United States, but direct-acting antiviral medications are now available and can cure the disease in over 95% of those that are treated. The Centers for Disease Control and Prevention (CDC) estimate that 75% of all chronic HCV infections in the United States are among adults born between 1945 and 1965. The CDC and US Preventive Services Task Force (USPTF) therefore recommends birth cohort screening for all adults born in this time period. In 2016, the Commonwealth of Pennsylvania signed into law a requirement that all hospitalized patients born during this time period be offered HCV screening. At two Penn Medicine hospitals, about 1000 eligible patients are admitted each month and despite an EHR alert that prompts ordering for eligible patients less than 20% are screened. In this study, we will conduct a stepped-wedge cluster randomized clinical trial to test the effect of defaulting HCV screening into the admission order set to improve screening rates.

## **2. Overall objectives**

The objective of the study is to evaluate the effect of a health system initiative setting defaults in the electronic health record admission order set to nudge inpatient HCV screening.

## **3. Aims**

### *3.1 Primary outcome*

The primary outcome measure is the change in percentage of eligible patients that receive HCV antibody screening.

### *3.2 Exploratory outcomes*

The exploratory outcomes include the change in the percentage of eligible patients who are viral load positive for HCV and who are HCV antibody positive. If data is available, we will explore the percentage of patients that have positive HCV testing who receive either linkage to care and/or HCV treatment

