## **5. Study design**

### *5.1 Design*

This study will use a stepped-wedge cluster randomized clinical trial to evaluate a health system initiative to improve inpatient HCV screening. We will randomly assign either the Hospital of the University of Pennsylvania (HUP) or Penn Presbyterian Medical Center (PPMC) to have the default intervention implemented in the admission order set within the electronic health record (EHR). Clinicians will have the opportunity to opt out and not order the screening test. There will be 3 wedges, each 3 months in duration, including a 3-month pre-intervention period, a 3-month period where only the site randomly selected to go first will have the intervention implemented, and then a 3-month period where both sites will have the intervention implemented. We will also look retrospectively at HCV screening rates before and after the EHR alert was implemented on May 14, 2019.

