### *5.4 Accrual*

Based on data from early 2020, we expect about 1500 patients per site over a three month period. Therefore, we estimate that for HCV screening, we will have 90% power to detect a 9.6-percentage point difference and 80% power to detect an 8.2 percentage point difference. This assumes a baseline rate of 20% and a 2-sided  $\alpha$  of 0.05 as our threshold for statistical significance. For detecting viral load positive patients, we estimate that we will have 90% power to detect a 3.7-percentage point increase and 80% power to detect a 2.9-percentage point

increase. This assumes a baseline rate of 0.5% and a 2-sided  $\alpha$  of 0.05 as our threshold for statistical significance.

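### Linkage to care and HCV treatment are given only as a percentage of test-positive patients, a group the default is meant to change, so a comparison between conditions need not track how many patients are linked

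*Protocol*

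**What the plan says.** Protocol Section 3.2 has two sentences. The first sets exploratory outcomes per eligible patient: the "change in the percentage of eligible patients who are viral load positive for HCV and who are HCV antibody positive". The second turns to linkage and treatment and changes the denominator: "we will explore the percentage of patients that have positive HCV testing who receive either linkage to care and/or HCV treatment". It is conditional on the data being obtainable. No linkage or treatment outcome per eligible patient is given.

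The primary outcome in Section 3.1 also counts all eligible patients: "the change in percentage of eligible patients that receive HCV antibody screening". The Abstract says the trial is to "test the effect of defaulting HCV screening into the admission order set to improve screening rates". Section 5.4 gives power for an increase in viral-load-positive patients from a baseline of 0.5%. Section 9 says all analyses are intention-to-treat with the patient as the unit, and describes a model for the primary outcome.

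**The concern.** A patient enters the linkage denominator only after being tested and found positive. Both happen after the hospital's condition is set, and testing is what the default changes. The positives found under the default therefore include patients who would not have been tested without it. They may differ from the others in how readily they are linked or treated.

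If the percentage is set against the no-default percentage, two differently formed groups are compared, and the intention-to-treat principle of Section 9 is lost for this outcome. The percentage also does not answer whether more patients reached care. Section 11.6.2 rests the study's benefit on finding patients who could be treated, so this outcome lies closest to that benefit and could be misread.

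**Working it through.** The protocol states no rate, effect or power for linkage or treatment, so there is no figure to reproduce. The check is whether the stated percentage follows the number of patients linked.

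**Inputs from Section 5.4:** 1500 eligible patients per site per quarter; baseline screening 20%; baseline viral-load positives 0.5%; detectable differences at 80% power of 8.2 points (screening) and 2.9 points (viral-load positive). The detectable differences serve only to set a scale and are not forecasts.

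**Assumed, because the protocol gives no value:** linkage rate L0 in positives who would be found anyway, and La in additional positives.

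**Formulas.** With P0 baseline positives and A additional positives:

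- number linked = P0·L0 + A·La
- percentage among positives = (P0·L0 + A·La) / (P0 + A)
- change in that percentage = A·(La − L0) / (P0 + A)

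The number linked rises whenever La > 0. The percentage falls if La < L0, is unchanged if La = L0, and rises if La > L0.

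**Positives per 1500 eligible.** Baseline: 0.005 × 1500 = 7.5.

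- Scenario (a), screening 20% to 28.2% at constant yield: 7.5 × 28.2/20 = 10.6, so A = 3.1.
- Scenario (b), viral-load positives 0.5% to 3.4%: 0.034 × 1500 = 51, so A = 43.5. This is an extreme case. Constant yield is 0.5/20 = 2.5% of those screened, so even universal screening would give only 2.5%. Scenario (b) therefore needs a higher yield.

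**Results with L0 = 60%.** At baseline 4.5 patients are linked: 60% of positives, 0.30% of eligible.

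| Scenario | La | Linked | Among positives | Among eligible |
|---|---|---|---|---|
| (a) | 30% | 5.4 | 51.3% | 0.36% |
| (a) | 60% | 6.3 | 60.0% | 0.42% |
| (a) | 90% | 7.3 | 68.7% | 0.48% |
| (b) | 30% | 17.6 | 34.4% | 1.17% |
| (b) | 60% | 30.6 | 60.0% | 2.04% |
| (b) | 90% | 43.7 | 85.6% | 2.91% |

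The first row of (a): 4.5 + 3.075 × 0.30 = 5.42; 5.42/10.575 = 51.3%; 5.42/1500 = 0.36%.

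**Other baseline linkage rates.** In scenario (b) with La = 20%, L0 = 40% falls to 22.9% while linked patients go from 3.0 to 11.7. L0 = 80% falls to 28.8% while linked patients go from 6.0 to 14.7.

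**Equal rates.** The percentage shows no effect although the number linked is multiplied by 10.575/7.5 = 1.41 in (a) and by 51/7.5 = 6.8 in (b).

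**Precision.** The design in Section 5.1 has three control hospital-quarters: both sites in the first period and one in the second. That is about 3 × 7.5 = 22.5 viral-load positives, so one patient moves the control percentage by about 1/22.5 = 4.4 points.

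**The case against.** The strongest reply is that no comparison between conditions is planned. The linkage sentence opens with "If data is available, we will explore" and, unlike the sentence before it, does not speak of a change. No model or test is named for it. Read that way it is a descriptive care-cascade step, and a legitimate one: are patients who are found then cared for? This largely stands, and it limits the point to any comparison between conditions. It does not supply a sound measure for that comparison if one is made.

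It can also be said that linkage per eligible patient is the product of positivity among eligible patients and linkage among positives. That is true as a crude figure, provided both use the same definition of positive. Section 3.2 does not settle this, since a positive test could mean antibody or viral load.

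A further reply is that the new denominator does not cure sparsity. That stands in full: the numerator is the same.

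A reader might infer something stronger, namely that selection and shorter follow-up both work against the default. The documents do not support this. Selection has no known direction without linkage rates. As for follow-up, intervention time does come later ("There will be 3 wedges, each 3 months in duration"), but no data cut-off or ascertainment rule is stated, so unequal follow-up would be an assumption. If the Section 9 model were applied, its period effects would largely absorb a difference that depends on admission date.

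**Conclusion.** The point holds in a limited form. The only linkage and treatment measure stated is conditional on a post-assignment result that the default is meant to change. If used to compare conditions, it is not an intention-to-treat contrast and need not move with the number of patients linked. On the protocol's planning figures and an assumed baseline linkage of 60%, it ranges from 51.3% to 68.7% in scenario (a) and from 34.4% to 85.6% in scenario (b) as the added patients' linkage goes from 30% to 90%. The number linked rises in every one of these cases.

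The size and sign rest on linkage rates that the protocol does not give, so no bias in a particular direction is shown. The wording does not establish that a tested comparison is planned. The outcome is exploratory, and the screening conclusion is unaffected. This is a worthwhile improvement, not an error that threatens the trial.

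**What to change.** Add to Section 3.2, as the exploratory measure for any comparison between conditions, the percentage of all eligible patients who test positive and are linked to care (or treated), counted over the same length of follow-up from admission in every period. Keep the percentage among positives as a descriptive care-cascade step, without a test between conditions.

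The cost is small. It is a change of wording to an exploratory outcome, and Section 8.2 already plans to collect HCV results and HCV medications. Linkage itself still depends on data being available. Extraction must wait until the last period has completed follow-up. Three 3-month periods take nine of the twelve months in Section 5.2, so follow-up longer than three months would run past the expected year. Linked patients will be few: about 7 to 8 viral-load positives per control hospital-quarter, fewer of them linked. The estimate should therefore be reported as imprecise whichever denominator is used.

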## **4. Background**

The hepatitis C virus (HCV) is the leading cause of liver transplant and hepatocellular carcinoma, but direct-acting antiviral medications are now available and can cure the disease in over 95% of those who are treated. The Centers for Disease Control and Prevention (CDC) estimate that 75% of all chronic HCV infections in the United States are among adults born between 1945 and 1965. The CDC and USPTF therefore recommends screening for all adults born in this time period. In 2016, the Commonwealth of Pennsylvania signed into law a requirement that all hospitalized patients born during this time period be offered HCV screening. At two Penn Medicine hospitals, about 1000 eligible patients are admitted each month and

despite an EHR alert that prompts ordering for eligible patients (implemented May 14, 2019) less than 20% are screened.

Defaults are the path of least resistance and often seen as an implicit recommendation. They are often fit better into clinician workflow because they do not require alerts or action to be taken. They are most appropriate when eligible patients can be accurately identified and defaults can be aligned with guidelines, in this case from the CDC, USPTF and Commonwealth of Pennsylvania. In prior work at Penn Medicine, we have used changes in defaults to increase generic prescribing, increase colorectal cancer screening, and decrease unnecessary imaging among palliative cancer patients.

## **5. Study design**

### *5.1 Design*

This study will use a stepped-wedge cluster randomized clinical trial to evaluate a health system initiative to improve inpatient HCV screening. We will randomly assign either the Hospital of the University of Pennsylvania (HUP) or Penn Presbyterian Medical Center (PPMC) to have the default intervention implemented in the admission order set within the electronic health record (EHR). Clinicians will have the opportunity to opt out and not order the screening test. There will be 3 wedges, each 3 months in duration, including a 3-month pre-intervention period, a 3-month period where only the site randomly selected to go first will have the intervention implemented, and then a 3-month period where both sites will have the intervention implemented. We will also look retrospectively at HCV screening rates before and after the EHR alert was implemented on May 14, 2019.

### *5.2 Study duration*

The study is expected to begin in September 2020 and take one year to complete.

### *5.3 Target population*

Adults born between 1945 and 1965 and admitted to either HUP or PPMC who have not already received HCV screening.

### *5.4 Accrual*

Based on data from early 2020, we expect about 1500 patients per site over a three month period. Therefore, we estimate that for HCV screening, we will have 90% power to detect a 9.6-percentage point difference and 80% power to detect an 8.2 percentage point difference. This assumes a baseline rate of 20% and a 2-sided  $\alpha$  of 0.05 as our threshold for statistical significance. For detecting viral load positive patients, we estimate that we will have 90% power to detect a 3.7-percentage point increase and 80% power to detect a 2.9-percentage point

increase. This assumes a baseline rate of 0.5% and a 2-sided  $\alpha$  of 0.05 as our threshold for statistical significance.

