## **9. Analysis plan**

All analyses will be conducted using intention-to-treat using the patient as the unit of analysis. All hypothesis tests will use a two-sided alpha of 0.05 as our threshold for statistical significance.

The primary outcome measure will use a binary indicator representing the presences of HCV screening or not for each patient. In the main adjusted analysis, we will fit models using generalized estimating equations using group (HUP or PPMC), period (3-month increment) fixed effects, and a variable for intervention (default implemented or not) and adjusting for temporal trends.

To test the robustness of our findings, we will perform sensitivity analyses that adjusts for available patient characteristics and comorbidities such as demographics and the Charlson Comorbidity Index.

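### The detectable differences in section 5.4 do not follow from the accrual, baseline rates and alpha given there; those inputs give clearly smaller differences for both screening and viral load

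*Protocol*

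**What the plan says.** Section 5.4 (Accrual) begins: "Based on data from early 2020, we expect about 1500 patients per site over a three month period". It presents the power statement as a consequence of that accrual: "we will have 90% power to detect a 9.6-percentage point difference and 80% power to detect an 8.2 percentage point difference". On the remaining inputs it says: "This assumes a baseline rate of 20% and a 2-sided" alpha of 0.05. For viral-load positivity it uses a 0.5% baseline and the same alpha, and gives 3.7 points at 90% power and 2.9 points at 80%. It mentions no intraclass correlation, design effect, loss of patients or power formula.

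Other sections fix the design and model. Section 5.1: "There will be 3 wedges, each 3 months in duration, including a 3-month pre-intervention period", followed by one period with the intervention at one hospital and one with it at both. Section 9 specifies "generalized estimating equations using group (HUP or PPMC), period (3-month increment) fixed effects, and a variable for intervention", and "All hypothesis tests will use a two-sided alpha of 0.05 as our threshold for statistical significance".

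The accrual figure agrees with section 4, where, for the two hospitals together, "about 1000 eligible patients are admitted each month": 1000 × 3 months ÷ 2 hospitals = 1500.

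**The concern.** With 1500 patients in each of six hospital-periods, a detectable difference of 8 to 10 points from a 20% baseline looks too large. Section 5.4 is the protocol's only sample-size justification, and it claims that the outputs follow from the inputs it prints. If they do not, either an input used in the calculation differs from the printed one, or the calculation contains an allowance for clustering that the reader cannot see. These two cases say different things about the trial. In the first, it has more power than claimed. In the second, its power rests on a parameter that is not stated.

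**Working it through.** **Inputs.** n = 1500 per hospital-period, baseline p1 = 0.20 (screening) or 0.005 (viral load), two-sided alpha 0.05 (all section 5.4); two hospitals by three periods, with exposure 0/1/1 and 0/0/1 (section 5.1); hospital effects, period effects and an intervention term (section 9). Normal quantiles: 1.960 for alpha, 0.842 for 80% power, 1.282 for 90%. I work on the risk-difference scale with independent patients, and let the period effects carry the adjustment for time trends.

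**Variance under the protocol's model.** The least-squares weights for the intervention effect on the six cell means are −½, 1, −½ in the hospital that goes first and ½, −1, ½ in the other. Their squares sum to 3, half from exposed and half from unexposed cells. So V = 3a/n, where a is the average of p1(1−p1) and p2(1−p2), and p2 = p1 + d. The detectable difference solves d = (1.960 + z) × √V.

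**Attempt to reproduce the stated figures at n = 1500.**
- Screening, 80%: p2 = 0.2523, a = 0.1743, √V = 0.01867, d = 2.802 × 0.01867 = **5.2 points** (stated 8.2).
- Screening, 90%: p2 = 0.2609, a = 0.1764, √V = 0.01878, d = 3.242 × 0.01878 = **6.1 points** (stated 9.6).
- Viral load, 80%: p2 = 0.0185, a = 0.01157, √V = 0.00481, d = **1.35 points** (stated 2.9).
- Viral load, 90%: p2 = 0.0215, a = 0.0130, √V = 0.00510, d = **1.65 points** (stated 3.7).

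**Other formulas for screening, n = 1500 (80% / 90%).**
- Two independent proportions, 1500 per group: 4.2 / 4.9 points.
- Random hospital effect with one exchangeable correlation: 4.2 / 4.9 at zero correlation, rising to a ceiling of 5.2 / 6.1 (the fixed-effects result).
- Difference-in-differences on the first two periods, V = [3p1(1−p1) + p2(1−p2)]/n: 5.9 / 6.9 points.

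None reaches 8.2 / 9.6.

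**Power at the stated screening differences, protocol's model, n = 1500.**
- d = 8.2 points: a = 0.1812, √V = 0.01904, 0.082/0.01904 − 1.960 = 2.35, power 99.1% (stated 80%).
- d = 9.6 points: a = 0.1842, √V = 0.01919, 0.096/0.01919 − 1.960 = 3.04, power 99.9% (stated 90%).

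**What the stated figures imply.** The implied standard error for screening is 0.082/2.802 = 0.0293 and 0.096/3.242 = 0.0296, so the two screening figures agree with each other.
- *As a cell size,* n = 3a/SE²: 635 and 630 patients per hospital-period for screening, and 529 and 521 for viral load. That is about 42% and 35% of 1500.
- *As a hospital-by-period SD with n = 1500,* √(SE²/3 − a/1500): at 8.2 points √(0.0002856 − 0.0001208) = 0.0128; at 9.6 points 0.0130. Both are about 1.3 points.
- *As a design effect on two proportions:* the stated screening differences need about 426 and 423 patients per group, so 1500/426 = 3.52 and 1500/423 = 3.55. Viral load needs about 356 and 350, so about 4.2 and 4.3. With 1500 per cluster, (design effect − 1)/1499 gives an intraclass correlation of about 0.0017 (screening) and 0.0021 to 0.0022 (viral load).

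**Sensitivity to a hospital-by-period SD (assumed values; the protocol gives none).** With V = 3(a/1500 + SD²), screening detects 5.2 / 6.1 points at SD 0, 7.2 / 8.4 at 1 point and 11.1 / 12.9 at 2 points.

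**The case against.** The strongest reply is that a cluster-randomised trial should allow for clustering, and that the larger stated differences may do exactly that. A two-proportion formula with a design effect of about 3.5 reproduces both screening figures, and one of about 4.2 to 4.3 reproduces both viral-load figures. The implied intraclass correlations are small and similar across the two outcomes, so this is a coherent explanation. Details of method may also sit in a statistical analysis plan that is not at hand. What stands of this: an allowance may have been used, and if so the fault is that it is not disclosed rather than a slip in arithmetic. What does not stand: section 5.4 lists its inputs and presents the figures as their result. A reader who follows it cannot arrive at them, whatever another document may contain.

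A second reply is that the error is harmless. On the stated inputs the trial has more power than claimed, and recruitment is set by calendar periods and all eligible admissions, so no patient number depends on the paragraph. This stands, and it limits the seriousness of the point.

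Two stronger readings are tempting. A reader might infer that 1500 was treated as the total per site over three periods, that is 500 per cell. The documents do not support this. Under the protocol's model 500 per cell gives 9.3 / 10.8 points for screening, not 8.2 / 9.6, and a match at 500 needs a random-hospital model with correlations that differ tenfold between the outcomes (0.0005 and 0.005). A reader might also infer that, cell size apart, only hospital-by-period variation could explain the figures. The design-effect route above shows otherwise.

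**Conclusion.** The point holds: all four detectable differences in section 5.4 fail to follow from its inputs. For screening the stated values exceed the recomputed ones by 3.0 points (8.2 against 5.2) and 3.5 points (9.6 against 6.1). For viral load they are a little more than twice as large. The cause cannot be determined from the document.

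The recomputation assumes independent patients given hospital and period, the risk-difference scale, equal cell sizes and a normal approximation, which is rough for a 0.5% event rate. The gap is too wide for these choices, or for the choice among the formulas tried, to explain it. It should not be read as evidence that the trial is too small: without hospital-by-period variation the stated figures are conservative, and the scenarios with such variation rest on assumed SDs. The point is of moderate weight: the justification is wrong as written and should be corrected, but no enrolment target, outcome, model or test changes with it.

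**What to change.** Restate section 5.4 so that the figures follow from what it prints, in one of two ways.

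1. If no allowance for hospital-by-period variation was intended, give about 5.2 / 6.1 points for screening and 1.35 / 1.65 points for viral load (80% / 90% power). Name the model (hospital and period effects) and the 1500 patients per hospital-period, and say that no such allowance is made.
2. If an allowance was intended, keep or recompute the figures and state the formula, the patients per hospital-period and the clustering parameter with its source. For example, a hospital-by-period SD of 1 point gives 7.2 / 8.4 points for screening and one of 2 points gives 11.1 / 12.9, both SDs being assumptions.

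In either case use the same method for both outcomes. The cost is a rewritten paragraph: no extra patients, and no change to the design or the analysis.
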